#### Health indicators

A set of physiologic biomarkers, motor function, health and pain perception, health services attendance and medication intake will be collected.

**Biomarkers** will be collected early in the morning and fasting by a licensed laboratory: (1) **blood pressure** measures the pressure with which the blood circulates within the arteries; **pulse** measures the count of arterial pulse per minute, the number of times the heart beats per minute; (2) **body weight** is assessed by weighing the person dressed in light clothing, without shoes and while fasting; (3) **Glycemia,** the amount of glucose present in the blood, used in the diagnosis and treatment of several diseases such as diabetes mellitus or hypoglycemia; (4) **Cholesterol (total),** a fatty substance produced by the liver, present in all body cells and essential for the formation of the cell membranes, digestion of fats, production of bile, metabolism of vitamins A, D, E and K, important in the constitution of global coronary disease risk; (5) **C-reactive protein (CRP),** a protein produced in the liver that in the case of inflammatory states increases in production. Indicates an ongoing, but not specific, organism infection. It can also be high in case of neoplasia; (6) **Erythrocyte Sedimentation Rate (ESR)** it is a measure of the red blood cells’ sedimentation by micro photometry over a period of time. A blood sedimentation rate is tested to detect inflammation in the body or to follow the progress of a disease.

**Respiratory Function (air volume and air speed)** will be measured by spirometry, using a portable spirometer (Medikro Pro). The air volume test consists of a simple examination, which allows to globally evaluate how the lungs are functioning by measuring the volume of air (measured in liters with the tests FVC, FEV1 and FEV6). In addition, the Tiffeneau-Pinelli Index will be measured, which is a ratio between FVC and FEV1. The air speed test consists of a simple examination, which allows to globally evaluate how the lungs are functioning by measuring the speed of air expired (litres per second, measured with the tests PEF, FEF 25 to 75%). Data is collected by trained researchers in motricity sciences.

**Body Balance** will be measured by the unipedal stance test. This test is suggested as a viable option, specifically when several measures or time constraints are in place (Whitney, Poole, & Cass, 1998) [72]. In this test the participant is instructed to balance on one foot of their choosing for up to 20 s. The number of seconds in balance is registered as the score of this test. Data collected by trained researchers in motricity sciences.

**Physical Activity** will be measured by actigraphy. The GT3X accelerometer that will be used in this study, is capable of recording accelerations in three axes (vertical, antero-posterior, and medio-lateral). Participants will be asked to wear the accelerometer around the hip for seven consecutive days (day and night, except when bathing). The accelerometer provides a measure of the frequency, intensity, and duration of physical activity and allows for the classification of activity levels as sedentary, light, moderate and vigorous [73].

**Sleep Quality** will be measured by actigraphy. The GT3X allows for a measure of the total duration of sleep of the subject [73]. The accelerometer provides a measure of the frequency, intensity, and duration of physical activity and allows for a measure of the total duration of sleep. Participants will carry the device with them at all times during a week, except when bathing.

**Pain Perception** is measured by the Brief Pain Inventory, adapted for the Portuguese by Ferreira-Valente, Pais-Ribeiro and Jensen (2009) [74]. Assesses different types of pain, including 9 questions: a first that is optional, a second one based on pain drawing diagrams, four items about pain intensity (worst pain, least pain, average pain, pain right now), two items on pain relief or medication, and one item on pain interference, with seven sub-items (general activity, mood, walking ability, normal walk, relations with other people, sleep, and enjoyment of life). Answering options vary between 0 ‘No pain/interfered’ and 10 ‘The greatest pain possible/completely interfered’.

**Health Status, Health Services Attendance and Medication Intake** – Data on the participants’ diagnosed diseases at baseline, the number and type of health services appointments, and medication intake during the various stages of the program will be registered by the Social Care Institution and provided to the research team with the authorization of the participants.

### Musical training and sensorial abilities

**Vocal Tuning Abilities** will be measured before and after the second intervention program through a test with two exercises. Notes (task 1) and chords (task 2) are played on a piano and participants are asked to sing the notes. Vocal tuning will be measured with an electronic tuner, indicating how close the vocal harmony was from the played note. One point is assigned for each correctly sung note, with a maximum score of 5 points in task 1 and of 6 points in task 2.

### Perceived motivation, expectations and benefits of participating in the program

The study also includes semi-structured interviews on the motivations, expectations and perceived benefits of participating in the program, positive and negative aspects of the program and suggestions for future programs. Also, the control group is asked about in which activities they participated while the first intervention was developing. The same will be asked to the experimental group in the follow up (see Fig. 3). Semi-structured interviews will be performed by researchers after all the other structured questionnaires and tests have been collected. The interviews will be recorded and verbatim transcribed. The content analysis will be performed after reducing the responses to minimal units of meaning, following a categorization by thematic coding according to the objectives of the interviews described above. Two researchers will work on the analysis independently, after which they will meet to discuss the analysis. Any disagreements in the content analysis of the interviews will be resolved through consensus.

All measurements are validated for the study population language with adequate psychometric properties. Additionally, the team will perform psychometric analysis of the measures in the study sample. Assessors will be trained for data collection with guidelines for instruments and measurement procedures, and for working with older adults. Data collection forms can be obtained upon request from the authors. Data entry and coding are subject to two rounds of verification by the peer assessors and by the PI.

Statistical methods include mean comparison of outcome measures (chi-square, t-test, general linear model for repeated measures analysis and ANOVA, after statistical assumptions are verified) between the three times of data collection (pre-test, post-test after 4 months and follow-up after 10 months) and between experimental and control groups. Two experimental sub-groups will be analyzed, as two intervention groups were formed, although with the exact same conditions. Additional, structural equation modelling analysis will be performed to test regression and mediation model hypothesis. No interim analyses are planned. Intention to treat strategies, imputing last observation carried forward, may be used.

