### Participants

Senior adults, users of the various services of the Santa Casa da Misericordia de Lisboa and Santa Casa da Misericordia de Almada (day-care centers, nursing homes and home care) will be invited by the staff of the institution to participate in an intervention and research program on singing groups. The Santa Casa da Misericordia (SCM) is a Portuguese social support institution whose mission is to improve the quality of life of the less privileged. The inclusion criteria for participants is being 60 years old or older, retired, accepting the invitation to participate in the program, and not having participated in other structured intervention programs in the previous 4 months. Exclusion criteria is having a severe diagnosed impairment that is an impediment for participating in the singing group activity (e.g. severe auditory, visual or mobility impairments). Sample Size. One hundred and forty participants will be invited to participate in the singing program and randomly assigned to an experimental (*n* = 70) or a waiting-list control (*n* = 70) group. A post hoc power analysis shows that this sample will be able to detect a large effect size (n2 = 0.14) with an 88% power. A dropout of 15 participants per group will reduce the study power to 79%. In order to promote adequate enrolment, transport will be provided for participants to attend the intervention sessions. To promote retention and complete follow up, the intervention team and the social support institution promote two social events related to the intervention program. An event for welcoming the second intervention group by the first intervention group will take place, with video presentations and singing together, and a final show with the participation of both intervention groups, after follow-up measurement.

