### Procedures and randomization

The social support institutions’ that are partners of the study will select potential participants, according to the eligibility criteria of the study and their records of the participants. All eligible older adults will be invited to participate in a singing group program, included in a scientific research study. A briefing will be organized by the research and intervention teams to answer the doubts of the potential participants and to explain the content of the informed consent. After the signing of the informed consent, pre-test measures will be collected, and randomization will be performed. The scientific coordinators of the study will set a numerical ordering of the list of participants and, using the SPSS randomization tool, will split up the participants into two equal groups. The social support institution will assign the selected participants to the intervention program. The participants, singing group facilitators and researchers conducting the study cannot be blinded to allocation. However, the collection of the data, namely, cognitive, psychosocial, motor and physiologic outcome measures will be assessed by independent researchers, blinded to group allocation (see Fig. 3).

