### Materials

The study aims to measure a set of biopsychosocial variables, described below, divided into four domains: psychoemotional, psychosocial, cognitive and health. All measures will be collected to measure change from baseline at 4 months (post-test) and at 10 months (follow-up).

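### No baseline-adjusted comparison at T1 is named: the listed tests either ignore the pre-test value or use it less efficiently than ANCOVA would

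*Protocol article*

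**What the plan says.** The statistical methods are given in one paragraph of the protocol article, at the end of the section on perceived motivation, expectations and benefits. They are said to include "mean comparison of outcome measures (chi-square, t-test, general linear model for repeated measures analysis and ANOVA, after statistical assumptions are verified", with comparisons made "between the three times of data collection (pre-test, post-test after 4 months and follow-up after 10 months) and between experimental and control groups". The paragraph does not say which listed method gives the main between-group result.

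Three other places bear on the point:
- **Procedures and randomization:** "After the signing of the informed consent, pre-test measures will be collected, and randomization will be performed". Baseline values therefore precede allocation.
- **Materials:** "All measures will be collected to measure change from baseline at 4 months (post-test) and at 10 months (follow-up".
- **Study design:** T0 to T1 is the randomized phase. T1 to T2 is described as non-randomized and compared within groups, because the control group has by then started the program.

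No section names ANCOVA, or the pre-test value of an outcome as a covariate.

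**The concern.** The trial pays for a full battery of pre-test measures in people with deliberately varied physical and psychological starting points. In a two-arm trial with a pre-randomization baseline, regressing the T1 value on arm and the T0 value is the standard way to turn those measures into precision. The list contains other analyses. Some ignore baseline. The other uses it with a fixed weight of one, when the data would usually support a smaller weight.

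What is at stake is precision and power on many outcomes, some of which may have effects well below the large one used for sample size. With no main method designated, the reader also cannot tell which level of precision the trial will deliver.

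**Working it through.** **Inputs from the article.** 140 participants ("One hundred and forty participants will be invited to participate in the singing program"), split evenly ("will split up the participants into two equal groups"), so 70 per arm. The dropout case loses 15 per arm, leaving 55. The stated capability is to "detect a large effect size (n2 = 0.14) with an 88% power", falling to 79% after dropout.

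**Assumptions, not in the article.** Two-sided alpha of 0.05; a T0–T1 correlation r, common to both arms; equal variance at T0 and T1; d = 0.40 as an example of a smaller effect.

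**1. The article's own power figures.** Eta-squared of 0.14 gives f² = 0.14/0.86 = 0.163 and, for two equal groups, d = 2f = 0.807. A two-group test then has power of 99.7% with 70 per arm and 98.7% with 55, not 88% and 79%. The stated pair agrees with itself at d of about 0.53 (88% and 79%). This mismatch is a separate matter. It is noted here because it determines how large the gain looks.

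**2. What each method does with baseline.** Per unit outcome variance, the relative variance v of the group difference is:
- T1-only t-test or ANOVA: v = 1.
- Group-by-time over T0 and T1: v = 2(1−r). This test is the change-score test. On simulated data the interaction F and the squared t on change scores were both 2.1242.
- ANCOVA: v = 1−r².

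The ANCOVA ratio is therefore 1−r² against T1-only and (1−r²)/[2(1−r)] = (1+r)/2 against change. Both are below 1 for any r strictly between 0 and 1. The change test beats T1-only only when r exceeds 0.5. A simulation at r = 0.6 gave 1.00, 0.78 and 0.64 (theory 1.00, 0.80, 0.64).

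| r | T1-only | Change | ANCOVA | ANCOVA / change |
|---|---|---|---|---|
| 0.4 | 1.00 | 1.20 | 0.84 | 0.70 |
| 0.5 | 1.00 | 1.00 | 0.75 | 0.75 |
| 0.6 | 1.00 | 0.80 | 0.64 | 0.80 |
| 0.7 | 1.00 | 0.60 | 0.51 | 0.85 |
| 0.9 | 1.00 | 0.20 | 0.19 | 0.95 |

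**3. Power at d = 0.40 with 55 per arm.** Noncentral t with 2n−2 = 108 degrees of freedom and noncentrality (d/√v)·√(n/2). Here √(55/2) = 5.244, so v = 1 gives 2.10, v = 0.75 gives 2.42, v = 0.60 gives 2.71 and v = 0.51 gives 2.94. The one degree of freedom spent on the covariate is ignored.

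| r | T1-only | Change | ANCOVA |
|---|---|---|---|
| 0.3 | 55% | 42% | 59% |
| 0.5 | 55% | 55% | 67% |
| 0.7 | 55% | 77% | 83% |

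**4. Sensitivity to the effect size.**
- At d of about 0.53, where the stated 88% and 79% agree, and r = 0.5, the same formula gives 79%, 79% and 89% with 55 per arm, and 88%, 88% and 95% with 70.
- At the stated eta-squared of 0.14 (d = 0.807), T1-only power is already 98.7% with 55 per arm and 99.7% with 70, so ANCOVA can add only about one point over it.

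**The case against.** The strongest reply is that the article does use baseline. The quoted list contains a repeated-measures general linear model, the time factor includes the pre-test, and the measures are said to capture change. That stands. A reader might infer that the plan compares raw post-test means and discards baseline, but the text does not support this. Nor does it say that a T1-only t-test is the main comparison.

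A second reply is that this is one paragraph of a journal article, that its list is introduced as what the methods include, and that covariates are commonly left to an analysis plan, which is not shown. This also carries weight, and nothing in the article excludes a baseline covariate. But the article goes beyond silence: it lists particular tests for the outcome comparisons, and ANCOVA is more precise than each of them for continuous outcomes.

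A third reply is that nothing here is biased. That is correct. One might infer that change scores carry a regression-to-the-mean artefact, but under randomization such regression is equal across arms in expectation. Only chance imbalance in the realized sample is handled less well, and that is a precision cost.

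Finally, the size depends on the assumed r and d. At r = 0.9 the gain over the change test is only 5% of variance, and at eta-squared 0.14 there is almost no power left to gain over T1-only.

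**Conclusion.** The point holds as one of efficiency, not as an error or a bias. No baseline-adjusted T1 comparison is named although the data for it are collected before allocation, and ANCOVA is more precise than either listed route at every r strictly between 0 and 1. For r from 0.4 to 0.7 it removes 15% to 30% of the variance of the group-by-time test and 16% to 49% of that of a T1-only test. The variance ratios rest on equal variances and an assumed r; the power figures also rest on an assumed d and alpha. The practical benefit is slight if effects are as large as the article supposes and useful if they are moderate.

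It should not be stretched to every outcome. Vocal tuning is measured only around the second program, and appointments and medication intake are records kept over the program's stages. These do not fit a single T0-adjusted model, and chi-square remains reasonable for categorical data.

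**What to change.** - For each continuous outcome measured at T0 and T1, name as the main randomized comparison an ANCOVA of the T1 value on arm with the T0 value of the same outcome as covariate, or a constrained longitudinal model. Report the adjusted mean difference with its 95% confidence interval.
- Keep methods suited to their type for count and categorical outcomes.
- Keep the three-time repeated-measures analysis as secondary, because the T1–T2 phase is not a randomized contrast.

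If an analysis plan already says this, a sentence pointing to it is enough. No extra data, visits or participants are needed; the cost is a few lines of wording, best settled before the T1 data are analysed.

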**WHAT:**	
**I Materials**:	
One rehearsal room with the capacity for 35 seated individuals and an additional 40 square meters for exercises and activities, one chair for each participant, one piano, one file with lyrics, one bottle of water for each participant, one separate coffee break room, transport for the older adults.	

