**WHERE**	
Sessions will be conducted in the rehearsal rooms of local theatres in Lisboa and Almada. The performance will take place in public theatres.	

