**WHEN and HOW MUCH**	
**Singing Program Duration:** 34 sessions, for about 4 months, 2 days a week, each with 2 h of group singing, with a 20-min break for socializing. **Participants:** Four groups of 30–35 participants.	

While the experimental group is participating in the intervention program, the control group will take part in the usual activities proposed by the day care centers (SCM), and these activities will be registered. After the experimental group finishes the program, the control group will enroll the exact same program. In time three of data collection, the same measures will be collected, representing a follow up for the participants of the first intervention group and a post-test for the second intervention group. All the financial costs of the intervention will be registered and information on all appointments attended in health care services and medication intake by the participants, during the period of implementation of the program, will be collected from both the social care institution and the participants. This will make it possible to calculate the difference between the costs of the program and the expected benefits of the program: for example, if significantly less health care services were used during the intervention periods and its estimated costs (e.g., medical appointments and hospital stays) were therefore lower.

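### The singing arm is taught in about two groups, but the named T1 tests and the power statement make no allowance for correlation within a singing group

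*Protocol article*

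**What the plan says.** - **Delivery.** Table 1 (WHEN and HOW MUCH) plans "Four groups of 30–35 participants". The Participants section allocates 70 to each arm, which gives about two groups per arm. Table 1 (WHERE) states: "Sessions will be conducted in the rehearsal rooms of local theatres in Lisboa and Almada".
- **Randomisation.** Individuals are allocated from one numbered list. The coordinators, "using the SPSS randomization tool, will split up the participants into two equal groups". No stratification by city is described.
- **Analysis.** The paragraph on statistical methods, at the end of the section on perceived motivation and benefits, lists chi-square, t-test, repeated-measures general linear model and ANOVA, plus structural equation models. It adds: "Two experimental sub-groups will be analyzed, as two intervention groups were formed, although with the exact same conditions". No term for singing group or city is named, and the sub-groups are not defined.
- **Power.** The Participants section says the sample is "able to detect a large effect size (n2 = 0.14) with an 88% power", falling to 79% if 15 per group drop out. Clustering is not mentioned.
- **Theory.** Psychosocial aspects (Background) expects choir work to build interdependence among members, and the hypotheses make social identification and loneliness mediators. In Table 1 each group chooses its repertoire after discussion and works through group dynamics towards a common goal.

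**The concern.** The mechanism the trial proposes is one that makes outcomes within a singing group correlate. A t-test or ANOVA on individuals treats the 70 singers as 70 independent pieces of information about the programme, although they come from about two realisations of it. If one group gels and the other does not, that difference is part of the uncertainty about what the programme does elsewhere, and these tests leave it out.

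At stake are intervals that are too narrow and a true error rate above the nominal 5%, for every outcome on which group effects vary. The plan tests many outcomes in four domains.

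**Working it through.** **1. The plan's own power figure.** Inputs (Participants section): 70 per arm, eta-squared 0.14. Assumed: two-sided 5%.
- f = sqrt(0.14/0.86) = 0.403; d = 2f = 0.807.
- An independent-samples test gives 99.7% power with 70 per arm and 98.7% with 55. The stated 88% and 79% do not reproduce.
- Both stated figures fit an independent-observations t-test at d of about 0.53 (87.6% and 78.7%). At eta-squared 0.14, an F test with 11 numerator degrees of freedom also comes close (89.9% and 78.3%). Neither calculation contains clustering. The mismatch is a separate matter; what counts here is that no reconstruction that comes close allows for singing groups.

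**2. Effect of clustering on the T1 comparison.** Inputs: m = 35 per singing group (Table 1, upper end); two groups in the experimental arm (arithmetic); controls not yet in singing groups, so one arm is clustered. The documents give no ICC, so a range is assumed.
- Design effect in the singing arm: DE = 1 + (m − 1) × ICC
- Variance ratio of the arm difference: (DE + 1)/2; SE ratio is its square root
- Actual error of the nominal 5% test: 2 × [1 − Φ(1.96/SE ratio)]

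| Assumed ICC | DE | Variance ratio | SE ratio | Error (formula) | Error (20,000 simulated trials) |
|---|---|---|---|---|---|
| 0.01 | 1.34 | 1.17 | 1.08 | 7% | 7.1% |
| 0.02 | 1.68 | 1.34 | 1.16 | 9% | 8.8% |
| 0.05 | 2.70 | 1.85 | 1.36 | 15% | 14.5% |

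At ICC 0 the simulation returned 5.1%. With 55 per arm after dropout (27.5 per group), the SE ratios are 1.06, 1.13 and 1.29, and the error 6.6%, 8.1% and 12.8%.

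**3. Power once the SE is corrected** (large-sample, 70 per arm, ICC 0.01 / 0.02 / 0.05). At d = 0.53: 83% / 77% / 64%. At eta-squared 0.14: 99% / 98% / 94%.

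**4. Can the trial estimate its own ICC?** With two singing groups, the between-group variance rests on one degree of freedom. Satterthwaite degrees of freedom for the arm difference are (DE + 1)² / (DE² + 1/69) = 3.0 / 2.5 / 1.9. That is too few for a usable estimate, so assumed ICCs are needed.

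**5. Comparisons in which both arms have sung.** Both arms are then clustered and the SE ratio is sqrt(DE) = 1.16 / 1.30 / 1.64.

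**6. Does ignoring city matter in the same way?** With 70 participants per city, simple randomisation, no clustering and a city difference of 0.5 or 1.0 SD, the simulated error of the test ignoring city was 5.2%. It does not.

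**The case against.** - **Individuals are randomised.** If singing affects nobody, the individual-level test keeps its nominal error. This stands. The inflation needs group-specific effects that vary, and a claim that goes beyond these two groups. The second condition is met in spirit, since the Discussion aims to validate the programme for older adults in general. The first is unknown, and for outcomes such as cholesterol or sedimentation rate the ICC may be near zero.
- **Shared staff.** Table 1 lists one maestro with a substitute and one pianist. Staff common to all groups create no between-group variance. This stands. Group-chosen content and social ties remain as sources.
- **A condensed article.** The list of methods is not presented as exhaustive, and model terms may sit in an analysis plan that is not shown. This stands in part. However, the article does name participant-level tests, and it recognises the separate groups without drawing a consequence for the analysis.

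Four stronger readings are tempting, and the documents do not support them:
- *That the unstratified split by city makes standard errors too small.* It risks chance imbalance and loses some precision; it neither biases the result nor understates the error (step 6).
- *That sub-group comparisons are not randomised.* The sub-groups are undefined. The text after Table 1 uses first and second intervention group for the immediate and waiting-list cohorts; on that reading T0 to T1 is the randomised contrast, and Study design already calls the later phase non-randomised. If they are cities, singers against controls of the same city remain a randomised comparison.
- *That the room for 35 will overflow and people will be moved after allocation.* The city split, the number finally enrolled and the placing of groups by city are not given.
- *That stratified randomisation is a free remedy.* The methods paragraph says groups were formed, so it may be too late.

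**Conclusion.** The point holds for singing-group clustering in the experimental arm at T1. The named tests and the power statement treat participants as independent, while the design and theory give reason to expect correlation. The standard error is understated by a factor of 1.08 to 1.36 and the 5% test runs at about 7% to 15%, for ICC 0.01 to 0.05. This rests on 35 per group, two groups whose membership stays broadly stable, effects that vary between groups, and inference beyond these groups. The ICCs are assumptions; with an ICC of zero nothing changes. The sub-groups also need a definition, because whether a comparison of them is randomised depends on it.

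This is a correction to make to the analysis, not a flaw that invalidates the trial: the randomised T1 contrast remains sound as an estimate.

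**What to change.** 1. Keep the T1 between-arm comparison as planned and add city (Lisboa or Almada) as a covariate. This is for precision only and does not replace step 2.
2. Report the T1 result again with the standard error multiplied by sqrt((DE + 1)/2), for a singing-group ICC of 0.01, 0.02 and 0.05 in the experimental arm, using the achieved group sizes. Where both arms have sung, apply the inflation to both, that is sqrt(DE).
3. In the Participants section, say that the power figure assumes independent participants.
4. Define the two experimental sub-groups. If they are singing groups or cities, compare each only with same-city controls, and label any sub-group against sub-group comparison as non-randomised.

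All of this uses data the trial already collects. The cost is wider intervals in the sensitivity analysis, by about 8%, 16% and 36% with 35 per group in one arm, and some results may no longer reach significance there.

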## Method

### Study design

The present study is a RCT with a crossover design with two conditions (experimental and control), where the participants will be randomly allocated to the two groups. Participants in the experimental group (EG) will take part in the singing group activity, while the control group will be involved in the usual social and artistic activities provided by the social support institution. Data collection will take place prior and after the singing group program and follow-up for the experimental group (6 months after the singing program has finished). The control group will participate in the program after the experimental group and post-test data has been collected from both groups. Semi-structured interviews on the motivations and perceived benefits of participating in the singing group will also be collected on the three times of data collection (see Fig. 2). In this study, we have an immediate intervention group (IG) and waiting-list control group (WLG). After the second assessment (T1), individuals in the control group will crossover to the intervention arm and participate in the singing group program. Thus, this study comprises a randomized experimental phase (T0 to T1 with a within- and a between-groups comparison) and a non-randomized quasi-experimental follow-up phase (T1 to T2 within groups comparison). We opted not to create a specific alternative activity for the control group individuals. Participants are instructed to maintain their daily usual social and leisure activities during the same period. All activities and the duration of the activities developed by the participants during the intervention program and the washout period will be registered for control.

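### Intention-to-treat is optional and last observation carried forward (LOCF) is the only imputation named, so the analysis set stays open and LOCF, if used, can bias the randomised comparison

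*Protocol article*

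**What the plan says.** The statistical-methods paragraph closes the section on perceived motivation, expectations and benefits. It lists tests of means, including "general linear model for repeated measures analysis and ANOVA, after statistical assumptions are verified", and attaches no analysis set to any of them. On intention-to-treat and missing data it says only: "Intention to treat strategies, imputing last observation carried forward, may be used". No condition decides when the option is taken, and no other part of the article names an analysis set or another way of handling missing values.

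The sections that determine what LOCF would do are these:

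- Study design: "this study comprises a randomized experimental phase (T0 to T1 with a within- and a between-groups comparison". The same section describes T1 to T2 as a non-randomised follow-up phase and says "After the second assessment (T1), individuals in the control group will crossover to the intervention arm".
- Materials: "All measures will be collected to measure change from baseline at 4 months (post-test) and at 10 months (follow-up".
- Participants (Sample Size): participants are "randomly assigned to an experimental (*n* = 70) or a waiting-list control (*n* = 70) group", and "A dropout of 15 participants per group will reduce the study power to 79" per cent. This is the only dropout figure in the article.

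**The concern.** There are two separate faults.

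**Open choice.** Because the wording is permissive, the team may analyse everyone randomised or only those who completed, and may decide outcome by outcome. The Materials section lists well over twenty outcomes, and Procedures and randomization says that the researchers conducting the study cannot be blinded to allocation. The Background says the protocol was registered to prevent selective outcome reporting, and an optional analysis set works against that aim. The trial's causal claim rests on comparing participants as randomised.

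**The method named.** For someone lost before T1 the only earlier value is baseline. LOCF therefore records a change of zero and treats it as observed. Health aspects says that ageing brings decline in functions such as breathing and balance, and the hypotheses expect the singing group to improve. Neither expectation fits a rule of no change. Dropout could also differ between arms, since one attends 34 two-hour sessions outside the day-care centres and the other keeps its usual activities.

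In the later, non-randomised phase, a waiting-list participant lost between T1 and T2 would have an untreated T1 value entered as the post-programme T2 value.

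**Working it through.** **Inputs from the article.** 70 per arm; dropout scenario of 15 per arm; randomised contrast T0 to T1.

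**Inputs assumed, because the article does not give them.** True effects, natural decline, unequal dropout, a T0-T1 correlation of 0.6, an outcome SD of 1 at each visit, and a two-sided 5% test on change scores.

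**Step 1: the article's dropout.** 15/70 = 21.4% per arm. The article's power figures (88%, and 79% after this dropout) do not enter the check. They also do not reproduce for a two-group test at eta-squared 0.14, which gives 99.7% with 70 per group and about 99% with 55. That is a separate matter.

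**Step 2: what LOCF estimates.** Let μT and μC be the mean changes among those observed, and pT and pC the proportions lost before T1. Each lost participant contributes zero, so

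LOCF estimate = (1 − pT)·μT − (1 − pC)·μC.

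**Step 3: equal dropout, p = 0.214.** The estimate becomes (1 − p)(μT − μC), whatever the common trend.

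- *Dropouts would have resembled completers in their arm.* The truth is μT − μC, so the effect shrinks by 21.4%. For 0.50 SD: 0.50 × 0.786 = 0.39 SD. For 0.20 SD: 0.20 × 0.786 = 0.16 SD.
- *Treated dropouts would have ended at control level.* The truth is (1 − p)μT + pμC − μC = (1 − p)(μT − μC), which is what LOCF estimates. Bias is zero.
- *No true effect.* μT = μC, so the estimate is zero at any decline and type I error stays at 5%.

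**Step 4: unequal dropout with no true effect (illustration).** Put μT = μC = −δ, pT = 0.30 and pC = 0.10. The estimate is −0.70δ + 0.90δ = +0.20δ, in favour of singing.

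The variance of an observed change is 2(1 − 0.6) = 0.8. Under LOCF the variance in an arm is (1 − p)·0.8 + p(1 − p)δ². The standard error is √[(VT + VC)/70]. Rejection is the two-tailed normal probability with mean estimate/SE.

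| Decline δ | False benefit | VT | VC | SE | Estimate/SE | Type I error |
|---|---|---|---|---|---|---|
| 0.1 SD | 0.02 SD | 0.562 | 0.721 | 0.135 | 0.15 | 5.3% |
| 0.3 SD | 0.06 SD | 0.579 | 0.728 | 0.137 | 0.44 | 7.2% |
| 0.5 SD | 0.10 SD | 0.613 | 0.743 | 0.139 | 0.72 | 11.1% |

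Simulation of the same design (40,000 runs per case) agrees: 5.2%, 7.5% and 11.4% in these three cases, and about 5.0% with 15 of 70 lost in each arm. It gives 0.39 SD for a true 0.50 SD in Step 3.

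**Step 5: a second unequal pattern.** With 21.4% lost in the singing arm, none in the control arm and no true effect, the estimate is +0.214δ. That is 0.04 SD for a decline of 0.2 SD and 0.09 SD for 0.4 SD.

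**The case against.** The best case for the plan has five parts.

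- **The dropout figure is not a forecast.** A reader might infer that 21% dropout is planned. The article uses 15 per group as a what-if for power, does not inflate the sample for it, and describes retention measures. This stands, and 21% is used here only as the level the article itself considers.
- **LOCF need not bias anything.** It acts only if the option is taken, and Step 3 shows a case with no bias. The 0.39 SD figure supposes that people who left would have gained the full benefit. This stands: LOCF can bias the result, and the direction depends on the balance and mechanism of dropout.
- **The false-positive figures rest on assumed inputs.** The article gives no rate of decline over 4 months and no unequal dropout. At its own equal dropout there is no false benefit, and what remains is attenuation, which works against the programme. This also stands, so the table is an illustration, shown with its small-decline row.
- **The harm of an open analysis set is not quantified.** True. In these calculations dropout is random, so completers are unbiased by construction. A reader might take that as support for a completer analysis, but it follows only from the assumption.
- **A separate analysis plan may settle the matter.** It may, and the article is condensed. But the article does not leave the point out: it addresses it, makes the key choice optional and names one weak method. The sentence needs correcting either way.

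The T2 problem lies outside the randomised comparison and is secondary.

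**Conclusion.** The point holds in a limited form. The article makes intention-to-treat optional, and that fault rests on the wording alone, with no numerical assumption. It names LOCF as the only imputation, and LOCF, if used, can bias the T0-T1 comparison.

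At 15 of 70 lost per arm, the cost is a 21% attenuation (0.50 to 0.39 SD) if dropouts would have resembled completers, and nothing if treated dropouts would have ended at control level. A false benefit of about 0.02 to 0.10 SD, with type I error of about 5% to 11%, needs both natural decline and heavier loss in the singing arm. Those inputs are assumed. The article does not support saying that LOCF will bias this trial, that 21% dropout is expected, or that type I error is inflated at the dropout it mentions.

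**What to change.** Replace the sentence with:

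> The primary analysis will include all randomised participants in the arm assigned, using a likelihood-based mixed model for repeated measures, or multiple imputation by arm from T0 outcomes and site, under missing-at-random. Completer and LOCF analyses, if done, are labelled sensitivity analyses.

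Choose between the mixed model and multiple imputation before outcome data are examined. Session attendance should not be an imputation variable at T1: it is recorded for the programme, and waiting-list controls have not yet entered it. A delta-adjusted sensitivity analysis is optional.

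The cost is a change of wording, standard software and a little more analysis work.
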